### 1.1. Ethical Considerations

This study has been ethically reviewed and approved by four institutional review boards: The Rwanda National Ethics Committee (Approval number: 332/RNEC/201), the University Teaching Hospital of Kigali Ethics Committee (Approval number: EC/CHUK/0111/2019), Rwanda Military Hospital Institutional Review Board (Approval number: RMH IRB/036/2019) and the University of KwaZulu Natal Biomedical Research Ethics Committee (Approval number: BE/280/19). All participants will sign a consent form (Additional File) prior to participation in the study.

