### 2.6. Phase 3: Cross Sectional Survey

#### 2.6.1. Objective 3: To assess HIVST Awareness among Men in Kigali, Rwanda

Design: A cross-sectional study will be employed. One health facility will be selected in each district. Due to the nature of the study design, and assuming that the population is >10,000 and that there is an unknown level of awareness of HIVST among men in Rwanda, the overall sample size will be deduced using the formula below:
(1)$$n=\frac{Z^{2}\times \;\mathrm{pq}\;}{d^{2}}$$
(2)$$n=\frac{1.96^{2}\times \left(0.5\right)\times \left(1-0.5\right)}{0.05^{2}}$$
where *n* = 384 participants.

For HIVST acceptability, assuming the acceptability rate of 94% reported in Kenya [45], the calculated sample size based on the formula above is 241 participants. For the purposes of this study, the desired sample size will be the highest of the two outcome variables. Sample size will not be adjusted for design effect as we will purposively select one tertiary facility in each district hence limiting the issue of error commitment during the recruitment. To determine the minimum sample size per facility, the probability proportionate to size will be used. A sampling frame for each study site will be developed based on the number of the out-patient departments’ male clinic attendees. Table 2 illustrates how sample size will be calculated for each study site and sampling strategy. Enrollment of participants will be by systematic random sampling. All men visiting the facility for the following reasons will be eligible to participate for the study (accompanying someone, visiting someone, or seeking health services). Healthcare workers will be excluded as they are considered implementers of HIVST thus expected to be knowledgeable on the intervention.

Data collection will be conducted using a self-administered semi-structured questionnaire (Supplementary File 2). The questionnaire will address demographic characteristics, health status and sexual behavior, health seeking behavior, and knowledge, attitudes, and perceptions (KAPs) toward HIVST.

Data Source: A semi-structured questionnaire will be employed.

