Analysis: Quantitative variables will be summarized by means and standard deviation. Qualitative variables will be summarized using frequency distribution. We will use the student t-test or the chi-square test to determine study variables associated with age awareness and the acceptability of HIVST. Univariate binary logistic regression analysis will be carried out to obtain preliminary insight into the unconditional association of each independent variable and dependent variables (awareness and acceptability). Multiple logistic regression will be employed to determine explanatory variables associated with awareness or acceptability status while adjusting for other study variables. All statistical tests will be concluded at a 5% level of significance employing Stata version 16 statistical package.

Outcome measures: We will assess two outcome measures: awareness and acceptability. Awareness will be considered as a yes response to the question “Do you know what HIVST is?”. Acceptability will be assessed by the question “As of 20 February 2017, it is recommended by the MOH to use HIVST kits as an additional strategy to reach out to people who are not yet tested, and there are plans for a national roll-out. Do you agree with this recommendation?”

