## 3. Data Security

The study will be conducted in accordance with the Helsinki Declaration [48]. Ethical approval to conduct this study was obtained from four relevant ethical committees. Study participants will be required to sign written informed consent prior to enrollment after the aim and objectives of the study have been explained and accepted by the participant, and participants will be provided with a copy of the consent form for future reference. Tape-recorded information and written data collected from participants on questionnaires will be stored appropriately in a lockable cabinet with restricted entry. Data obtained will also be captured in statistical software on a password-protected laptop. The transfer of data across the research team will occur via an encrypted flash drive or a secure file transfer protocol. Information provided by participants will be kept anonymous. Data will be kept anonymous during the study and will be kept strictly confidential in storage for two years after the completion of the study within the University of KwaZulu Natal. During the dissemination of the findings, no identifying data will be made public. Therefore, the researcher will take responsibility to ensure that, even after all information has been collected, sources will never be identified.

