## 4. Discussion

The aim of this study is to adapt an HEP for improving the uptake of HIVST by men in Rwanda. To the best of our knowledge, this study is the first of its kind in Rwanda. Given the reported low uptake of HTSs among men in Rwanda, and in Sub-Saharan Africa in general, implementing an effective HEP to improve the uptake of HIVST, a new intervention with reported acceptability among men, may help bridge this gap. The pragmatic approach is designed to provide results that are directly applicable to normal practice.

Several studies have called for the need for the implementation of policies that advocate for men’s health [49,50,51]. Tailored HEPs to improve men’s uptake of HTSs have been recommended [52]. As HIVST is relatively new in Rwanda [11], there is need for the implementation of guidelines and policies that advocate for men’s engagement in this new intervention and for the scaling up thereof [53]. The knowledge obtained by the present study may thus guide HIVST implementation in Rwanda with the potential of being further incorporated into routine practice.

Consistent with the nature of pragmatic trials, we aim to influence policy by providing stakeholders with results that are applicable to routine practice. We intend to disseminate findings of the study through reports, publications in peer-reviewed journals, research meetings, and conference presentations.

Due to constraints of time and resources, as this study is for a doctoral degree with limited findings, a pilot RCT will be used to assess the preliminary effects of the HEP. A pilot study is not a hypothesis testing study. However, a pilot study is a requisite initial step, and results can inform feasibility and identify modifications needed in the design of a larger ensuing hypothesis-testing study. In this study, the feasibility of recruitment, intervention implementation, and retention will be examined. Secondly, due to the nature of the HIVST being conducted privately, study outcomes will be based on self-reported data. Finally, the HIVST uptake is only as important as the number of individuals actively linked to care and treatment services. The proposed study will not actively follow up on participants for linkage to care and treatment services. However, sufficient information on linkage to care post-HIVST will be provided on both enrollment and follow-up visits.

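### The Phase 3 awareness item has no 'before today' reference and follows a consent talk about HIVST, so the awareness estimate is open to upward bias of unknown size (minor)

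*Protocol article*

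**What the plan says.** The outcome rule in section 2.6.1 of the protocol article is complete as written: "Awareness will be considered as a yes response to the question" whether the man knows what HIVST is, and nothing further qualifies it. No time reference is attached and no other item enters the definition.

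Two places put consent ahead of the questionnaire. Section 1.1 says "All participants will sign a consent form (Additional File) prior to participation in the study". Section 3 says participants must "sign written informed consent prior to enrollment after the aim and objectives of the study have been explained and accepted by the participant". HIVST is named in what would be explained: the Discussion states "The aim of this study is to adapt an HEP for improving the uptake of HIVST by men in Rwanda", and the survey's own objective reads "Objective 3: To assess HIVST Awareness among Men in Kigali, Rwanda".

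The self-administered questionnaire also covers "knowledge, attitudes, and perceptions (KAPs) toward HIVST". Table 3 lists knowledge among the factors to be related to awareness by logistic regression. The questionnaire itself (Supplementary File 2) and the consent form (Additional File) are not shown.

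**The concern.** The survey is meant to describe what men in Kigali already know about self-testing. A present-tense question put after a consent talk about an HIVST study measures something slightly different: what the man knows by the time he answers. A man who first met the idea minutes earlier can truthfully say yes, and nothing in the definition marks him out.

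Three uses of the figure are affected. Awareness is the outcome that sets the survey size at 384. It is a dependent variable in the univariate and multiple logistic regressions. The survey is also one of three inputs to the nominal group that shapes the health education program. The article treats lack of awareness as a barrier to uptake (Background; section 2.9), so an inflated figure would make that barrier look smaller than it is. A larger sample would not help, because this is not sampling error.

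**Working it through.** **Step 1. The plan's own figure.** Section 2.6.1 uses n = Z²pq/d² with Z = 1.96, p = 0.5, d = 0.05:

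3.8416 × 0.25 / 0.0025 = 384.16, which reproduces the stated 384. This sizes the survey for a 95% margin of ±5 points and covers sampling error only.

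**Step 2. The order of events.** Consent precedes participation (1.1), the aim and objectives are explained before signature (3), and both the aim (4) and the survey objective (2.6.1) name HIVST. Every respondent has therefore met the term before answering. Whether he has also been told what it means depends on a consent form that is not shown.

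**Step 3. A bias model.** Two inputs are needed, and the documents give neither, so both are assumed:
- a = true awareness before study contact;
- f = share of previously unaware men who answer yes because of the consent talk.

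Expected measured awareness = a + (1 − a)f, so bias = (1 − a)f.

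**Step 4. When the bias exceeds the planned margin.** (1 − a)f > 0.05 when f > 0.05/(1 − a):
- a = 10%: 0.05/0.90 = 5.6%
- a = 20%: 0.05/0.80 = 6.3%
- a = 40%: 0.05/0.60 = 8.3%

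**Step 5. Effect on the confidence interval at n = 384.** With o = a + (1 − a)f and SE = √(o(1 − o)/384), the half-width is 1.96 × SE. Normal-approximation coverage of the true a is Φ(1.96 − bias/SE) − Φ(−1.96 − bias/SE).

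| a | f | Measured | Bias (points) | Half-width (points) | Coverage |
|---|---|---|---|---|---|
| 10% | 5% | 14.5% | 4.5 | 3.5 | 29% |
| 10% | 10% | 19% | 9 | 3.9 | under 1% |
| 30% | 5% | 33.5% | 3.5 | 4.7 | 69% |
| 30% | 10% | 37% | 7 | 4.8 | 19% |
| 50% | 2% | 51% | 1 | 5.0 | 93% |
| 50% | 10% | 55% | 5 | 5.0 | 50% |

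At f = 0 the bias is zero and coverage is nominal. The table shows how large f would have to be to matter. It is not evidence of what f is.

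**The case against.** The strongest reply is that naming a topic does not teach it. The item asks whether the man knows what HIVST is, which is more than having heard of it. A man who has just met the term in a consent talk may honestly answer no. With the consent wording and item order unseen, f could be negligible. This stands, and it is why the point concerns what the definition leaves open.

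A reader might infer that awareness will be overstated and that all error in the item runs upward. The documents do not support either. Consent exposure alone can only raise the figure, but a man who knows of self-testing without knowing the term or its abbreviation would answer no, which pulls the other way.

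A reader might also want the primary definition to require a correct knowledge answer. That would build a factor that Table 3 lists as explanatory for awareness into the outcome itself, and make their association partly circular. Collecting knowledge separately, as the plan does, is defensible.

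Finally, the consequences are limited. Table 3 sets no success criterion for awareness, Phase 4 does not depend on the figure, the premise in section 2.9 rests on a separate cited source, and the nominal group also draws on a scoping review and stakeholder interviews. This stands too and keeps the severity low. None of it supplies a way to tell prior awareness from awareness gained at consent.

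**Conclusion.** The concern holds as a minor weakness of measurement. As defined, the awareness outcome cannot distinguish knowledge held before study contact from knowledge gained at consent, and so admits upward bias by a route that the article itself documents. The size cannot be computed from the documents. Under the assumed model, a false-yes share of roughly 6% to 8% among unaware men would match the planned 5-point margin if prior awareness lies between 10% and 40%; at f = 0 there is no bias. The conclusion rests on the order of consent and questionnaire stated in sections 1.1 and 3, and on the definition in section 2.6.1 being the whole rule. It does not establish that the survey result will be wrong, nor that any later decision in the project would change.

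**What to change.** Anchor the item to the time before study contact and spell the term out, for example: *Before today, did you know what HIV self-testing is?* Place it ahead of all other HIVST content in the questionnaire, including the acceptability statement, once the present order has been checked against Supplementary File 2.

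Keep the primary definition as a yes to this item alone. If Supplementary File 2 holds a suitable knowledge question, a knowledge-confirmed proportion may be reported beside it as a descriptive sensitivity figure, but not as the outcome of the regression.

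The cost is one reworded item and possibly a change of order, with no extra participants or staff. Results would be less directly comparable with surveys that use the present wording, and the awareness figure would probably come out somewhat lower.

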### 2.9. Phase 4: Pilot Randomized-Controlled Trial

Objective 5: HIVST was officially introduced on World AIDS Day in 2017 in Rwanda [46]. Since then, HIVST guidelines have been included in the national HIV prevention and management guidelines as of 1 July, 2018 [47]. Available evidence show a lack of awareness of HIVST among men in Kigali [28]. In this phase, we will aim to determine the preliminary effectiveness of the HEP on the uptake of HIVST among men in Rwanda and assess the feasibility of conducting a larger trial.

Design: The pilot RCT protocol is registered with the Pan African Clinical Trial Registry (Registration: PACTR201908758321490). We will conduct a two-arm pilot RCT. Participants will be randomized to the HEP arm or the control arm. In the control group, routine health education will be administered. In the intervention group, the adapted HEP will be administered in addition to routine health education. Data collection will be through interviewer-administered questionnaire captured onto mobile tablet devices using pre-programmed study software Open Data Kit.

Recruitment strategy: The University Teaching Hospital of Kigali (CHUK) will be purposively selected to pilot the implementation of the HEP intervention. CHUK is the largest hospital located in the district of Nyarugenge, Kigali. It is also the largest referral hospital in the country with a capacity of 519 beds. In 2017, the hospital recorded 140,559 patients with an average of 11,713 per month [11]. The PI of the study will introduce the intervention in the out-patients’ department, as these individuals are not expected to have critical conditions that would affect their ability to take part in the HEP or the interviewer-administered questionnaire. Trained health care professionals will administer the HEP to eligible participants. In this study, we will include participants who fit the following criteria:is an adult man 18 years and older;does not know his HIV status;is visiting the study-selected health facility during the enrollment periodis willing to be followed up three months post-enrollment.

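### The survey's acceptability outcome is one leading question about a Ministry policy, so it records endorsement of the policy and not a man's own willingness to self-test

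*Protocol article*

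**What the plan says.** Section 2.6.1 (Objective 3) states: "We will assess two outcome measures: awareness and acceptability". Awareness is a yes to a direct question on whether the man knows what HIVST is. Acceptability is one question, given in full. Its stem reads in part "it is recommended by the MOH to use HIVST kits as an additional strategy to reach out to people who are not yet tested", and it closes with "there are plans for a national roll-out. Do you agree with this recommendation". No other section redefines the outcome.

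The same section makes acceptability a dependent variable in the univariate and multiple logistic regressions, and Table 3 lists it beside awareness. Section 2.6.2 (Objective 4) uses the survey's awareness and acceptability results, with the scoping review and the stakeholder interviews, to guide the nominal group that develops the health education programme.

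The self-administered questionnaire also covers "health seeking behavior, and knowledge, attitudes, and perceptions (KAPs) toward HIVST", but those items are not used to define acceptability. For sample size, the section gives 384 for awareness and 241 for acceptability, "assuming the acceptability rate of 94% reported in Kenya", and takes the larger.

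**The concern.** Two features of the item are at issue.

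- **Construct.** A man can think it sensible for the Ministry to offer kits to untested people and still not want to use one. The reverse is also possible. The item asks only for the first opinion.
- **Form.** The stem names the health authority and announces a planned roll-out before asking for agreement, which invites a yes.

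What is at stake is whether the survey answers its own question. The programme is meant to improve men's own uptake, and Section 2.9 (Phase 4) measures uptake as self-reported use of a kit. If acceptability means agreement with a policy, the reported proportion and the factors associated with it describe something other than the behaviour the programme is meant to change. This cannot be repaired after data collection unless another item happens to ask about personal use.

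**Working it through.** **1. The item set against its purpose**

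| Element | What the protocol article fixes | Where |
|---|---|---|
| What is asked | Agreement with a Ministry recommendation | 2.6.1, Outcome measures |
| Whom the recommendation concerns | People not yet tested | 2.6.1, Outcome measures |
| Who answers | All men at the facility as patients, visitors or companions; healthcare workers excluded | 2.6.1, Design |
| Use in analysis | Dependent variable in logistic regression | 2.6.1, Analysis; Table 3 |
| Use in development | One of three inputs to the nominal group | 2.6.2 |
| Target behaviour | Men's own use of a kit | 2.9 |

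No eligibility rule excludes men who have already been tested. For them the recommendation concerns other people. For a man unaware of HIVST, the only information within the item is its purpose and the Ministry's endorsement. In both cases a yes says little about his own intention.

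**2. The protocol's sample sizes**

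The formula is n = Z² × p × (1 − p) / d², with Z = 1.96.

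- Awareness, p = 0.5, d = 0.05: 3.8416 × 0.25 / 0.0025 = 384.2. This reproduces 384.
- Acceptability, p = 0.94, d = 0.05: 3.8416 × 0.0564 / 0.0025 = 86.7. This does not reproduce 241.
- Acceptability, p = 0.94, d = 0.03: 3.8416 × 0.0564 / 0.0009 = 240.7. This reproduces 241, so the figure implies a margin of 3 points.

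**3. What a change of item does to precision**

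At n = 384 the 95% half-width is 1.96 × √(p(1 − p)/384): 2.4 points at p = 0.94, 4.0 at 0.80, 4.9 at 0.60 and 5.0 at 0.50. A 5-point margin is therefore met, to rounding, at any p. For a 3-point margin:

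- p = 0.90: 3.8416 × 0.09 / 0.0009 = 384.
- p = 0.80: 3.8416 × 0.16 / 0.0009 = 683.

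The 3-point margin thus holds at 384 only if willingness is about 90% or more.

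**4. Why sample size does not help (illustration on assumed values only)**

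Let w be true willingness and a the share of unwilling men who still agree with the policy, and suppose every willing man agrees. Measured acceptability is w + (1 − w)a, so the error is (1 − w)a.

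- w = 0.80, a = 0.25: 0.80 + 0.20 × 0.25 = 0.85, an error of 5 points.
- w = 0.60, a = 0.75: 0.60 + 0.40 × 0.75 = 0.90, an error of 30 points.

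The error does not depend on n. Neither w nor a is in the documents, so the spread of 5 to 30 points shows only how much rests on unknowns. It is not an estimate.

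**The case against.** The best defence is that the damage is contained, and much of it stands. The questionnaire has knowledge, attitude and perception items, and Supplementary File 2 is not shown, so personal-use questions may exist. The survey is one of three inputs to a nominal group that generates its own ideas, ranks barriers and includes four men from the target population. Phase 4 measures kit use directly, and no trial outcome depends on this item. Self-administration may reduce pressure to please an interviewer, though it leaves the stem unchanged.

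The defence also rules out several stronger readings that a reader might infer:

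- **That the whole survey measures deference to policy.** The criticism applies to one outcome definition. Deference is an inference about how men will respond.
- **That agreement will sit near 100%.** Nothing in the documents gives a response rate for this item.
- **That the wording leaves too few negative answers for the regression.** At the 94% planning rate, 384 × 0.06 = 23 men would answer no. That follows from the rate, and a neutral item with the same rate would give the same 23. The documents do not say what question produced the Kenyan figure.
- **That the dates contradict each other.** The stem begins "As of 20 February 2017, it is recommended by the MOH to use HIVST kits as an additional strategy to reach out to people", while Section 2.9 says "HIVST was officially introduced on World AIDS Day in 2017 in Rwanda" and places HIVST in national guidelines from July 2018. These events are in sequence, and introduction is not completed national roll-out. The stem is dated, which is a lesser fault.

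None of this changes what the item asks. The protocol makes it the definition of acceptability, and it is silent on the man's own willingness.

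**Conclusion.** The point holds for the acceptability outcome. Followed exactly, Section 2.6.1 records endorsement of a Ministry policy through a leading question and reports it as acceptability of HIVST. Agreement may overstate men's willingness to use a kit. The size cannot be estimated from the documents, and even the direction rests on the judgement that more unwilling men will agree than willing men will disagree. The mismatch between the item and its purpose needs no such assumption, since it is plain from the wording.

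The change is worth making before the survey because it is cheap then and probably impossible afterwards. It does not threaten the Phase 4 trial, the awareness outcome or the governing sample size.

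**What to change.** Define acceptability by a neutral item on personal use, for example *Would you be willing to use an HIV self-test kit yourself?* with answers yes, no and unsure. Place it after the awareness item and after a short neutral description of HIVST that omits the Ministry statement. State in advance how unsure is coded, because the planned regression needs a binary outcome. Keep the policy question as a separately labelled secondary item, placed later, with its stem updated in line with Section 2.9. This preserves comparison with any source that used the policy wording.

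If Supplementary File 2 already holds a suitable personal-use item, naming it as the acceptability outcome would suffice.

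The cost is one added or reworded question and an amendment to the ethics committees; Section 1.1 lists four. The sample size stays at 384, governed by awareness at p = 0.5. The protocol should also state the margin intended for acceptability. If it is the 3 points implied by 241, the text should acknowledge that 384 will not deliver it when willingness is below about 90%.
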